#### Blinding

Only osteopaths, their accompanying persons, and a psychologist coordinator ([name]) will receive information about group allocation, as well as patients and parents when the patient is under 18. The assessor of the clinical and psychological outcomes (research psychologist) will be blinded from the treatment group and will use standardized research questionnaires. Assessors of the osteopathic outcomes will not perform the osteopathic sessions, to guarantee an independent evaluation.

### Interventions

After their inclusion in the trial, the patients will receive either the targeted osteopathic treatment in addition to TAU (group A) or TAU alone (group B).

#### Osteopathic treatment (group A)

Special attention is paid to body approach care for anorexic patients in our psychiatry unit. A targeted osteopathic treatment for AN has been created by an osteopath ([name]), based on scientific literature and her own experience. The protocol was refined after 3 sessions for 3 different patients during the preparatory phase of the study. Indeed, in May 2019, 3 sessions of the osteopathic protocol were performed 1 week apart for 3 patients hospitalized in the department of psychiatry, after medical advice of no contraindication to the practice. The consent agreements of patients and their parents were collected and included in their medical records. Each intervention took place in full view of a caregiver of the unit as we usually do.

The osteopath, [name], trained and supervised a group of osteopath students specially dedicated to the protocol, in their 3rd and 4th year of school.

Each patient allocated to group A will be followed by the same two osteopaths. One of them will provide the 5 sessions of osteopathic treatment. Sessions have a 30-min duration and about a week separates two sessions. The other one will evaluate the evolution of the somatic dysfunction. Two caregivers of the service will attend the sessions with the osteopaths and the patient. The presence of a caregiver during the therapeutic activities is customary in our unit.

The osteopathic treatment protocol will use techniques on 3 areas: cervical, diaphragmatic, and digestive. The protocol is detailed in Additional file 2.

#### TAU (for groups A and B)

The outpatient and inpatient treatment will be done in accordance with the French Health Authorities’ recommendations [11]. Multidisciplinary care is proposed, possibly involving nurses, psychologists, psychiatrists, general practitioners, gynecologists, rheumatologists, dieticians, occupational therapists, body approach specialists, and social workers. Targets for treatment include ED symptomatology, consequences of starvation, psychological disorders, and family interactions. A coordinating psychiatrist coordinates the care for AN. For a full description of inpatient and outpatient treatment modalities in our structure, see previous studies [29–31].

### Instruments

Figure 2 summarizes the patients evaluations proposed at baseline, before the 3rd osteopathic session (group A) or 3 weeks after the first questionnaires (group B) and 1 week after the last osteopathic session (group A) or 6 weeks after the first questionnaires (group B).

**Fig. 2 Fig2:**
[figure not shown]
Schedule of enrolment, interventions and assessments for ACAMTO study (SPIRIT figure). Legend: AUT = as usual treatment; BSQ = Body Shape Questionnaire; BVAQ-B = Bermond-Vorst Alexithymia Questionnaire Form B; DEQ = Depressive Experiences Questionnaire; ED-QOL = Eating Disorders Quality Of Life Scale; EDDS = Eating Disorder Diagnostic Scale; EDI-2 = Eating Disorders Inventory-2; EDS-R = Exercise-Dependence Scale-Revised; fMAIA = French Multidimensional assessment of Interoceptive Awareness; HAD = Hospital Anxiety and Depression scale; OSI = Ottawa Self-Injury Questionnaire; RSE = Rosenberg Self-Esteem Scale; Short-CIDI = Short-Composite International Diagnosis Interview; SOAP = Subjective, Objective, Assessment, Plan; STAI-Y = State-Trait Anxiety Inventory, Form Y. *The SOAP note form is assessed during the study period before each osteopathic treatment sessions and at T3

Evaluations are described in the following paragraphs.

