### Secondary objectives

Secondary objectives are as follows:
To examine if adding a targeted osteopathic treatment to TAU for AN is significantly more efficacious than TAU alone in terms of clinical evolution, evaluated by other clinical outcomes (self-esteem, anxiety, depression, depressivity, alexithymia, quality of life, ED symptoms, physical hyperactivity, self-injury, body satisfaction, body mass index).To assess if adding a targeted osteopathic treatment to TAU for AN compared to TAU alone is significantly more efficacious in terms of the evolution of somatic dysfunctions (sensitivity, mobility, texture, asymmetry).To explore the subjective experience of patients who have completed osteopathic treatment sessions.To explore the subjective experience of osteopath students who have performed the osteopathic treatment sessions.

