#### Secondary outcomes

Secondary outcomes are as follows:
Change in the patient’s overall clinical outcome (weight, pain, transit…) from T1 (baseline) to T3 (1 week after the last osteopathic session (group A) or 6 weeks after the first questionnaires (group B)).Change in the nature and severity of patient’s ED symptoms (EDDS and EDI-2) from T1 to T3.Change in the nature and severity of patient’s psychopathological symptoms (BSQ, BVAQ, RSE, STAI-Y, DEQ, HAD, OSI, EDS-R) from T1 to T3.Change in the perceived quality of life (ED-QOL) from T1 to T3.Change in somatic dysfunction (SOAP note form) from T1 to T3.Qualitative analysis of interviews of patients who received osteopathic treatment and osteopath students that performed the sessions (Interpretative Phenomenological Analysis method).

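### The between-arm test of somatic dysfunction (SOAP) rests on ratings by osteopaths who know the allocation, and the text describes SOAP timing and rater only through group A

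*Protocol article*

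**What the plan says.** **The comparison.** Secondary objectives asks whether adding osteopathy to usual treatment is "significantly more efficacious in terms of the evolution of somatic dysfunctions (sensitivity, mobility, texture, asymmetry"). Secondary outcomes defines the endpoint as "Change in somatic dysfunction (SOAP note form) from T1 to T3", without limiting it to one arm. Statistical methods includes this change among the variables compared by Student's t test or the Mann-Whitney test, two-sided at 0.05.

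**The timing.** The legend to Fig. 2 says: "The SOAP note form is assessed during the study period before each osteopathic treatment sessions and at T3".

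**The rater.** Under Osteopathic treatment (group A): "Each patient allocated to group A will be followed by the same two osteopaths". One of them treats. Of the second it says: "The other one will evaluate the evolution of the somatic dysfunction".

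**Who knows the arm.** Blinding begins its list of those told the allocation with "Only osteopaths, their accompanying persons, and a psychologist coordinator", and adds patients and, for minors, parents. For the questionnaires, "The assessor of the clinical and psychological outcomes (research psychologist) will be blinded from the treatment group". For the osteopathic outcomes the safeguard is different: "Assessors of the osteopathic outcomes will not perform the osteopathic sessions, to guarantee an independent evaluation".

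**The concern.** SOAP is the outcome closest to the intervention's own theory, and it depends on an examiner's judgement of sensitivity, mobility, texture and asymmetry. A between-arm test of such a rating is only as good as the examiner's ignorance of the arm. Here the safeguard is that the examiner does not treat, which is a different thing.

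There is also a mismatch between the test and the measurement plan. A comparison of T1-to-T3 change needs a T1 and a T3 rating in both arms, obtained in the same way. The readable text ties the ratings to group A's sessions and group A's osteopath pair. A positive SOAP result could then reflect what the rater knew, or how often and by whom patients were examined, as easily as an effect of treatment.

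**Working it through.** The main point is settled by setting the sections side by side. The arithmetic only shows how sensitive the test is.

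**1. Is the rater blinded?**
- The group A rater is an osteopath (Osteopathic treatment section).
- Osteopaths are told the allocation (Blinding section).
- A form completed just before an osteopathic session also shows by its timing that the patient is in group A.
- The Blinding section uses the word for blinded of the research psychologist only. For the osteopathic outcomes it claims independence on the ground that the rater does not treat.

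So the group A rater knows the arm. If T1 in group A is the form completed before session 1, both ends of the change score are rated with that knowledge. This step does not need Fig. 2.

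The Discussion names bias linked to the osteopath students as a challenge. Its answer is training and communication with the osteopath who developed the treatment, which does not address knowledge of the arm.

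**2. Does the measurement plan match the test?**

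| | Group A | Group B |
|---|---|---|
| Needed for the test | T1 and T3 | T1 and T3 |
| Written timing (Fig. 2 legend) | before each of 5 sessions, and T3 | T3; no sessions to anchor anything earlier |
| Written rater | second osteopath of the pair | none named |

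Read literally, group A has 5 + 1 = 6 examinations and group B has 1. If Fig. 2 marks a T1 SOAP in both arms and T1 in group A is the pre-session-1 form, the counts become 6 and 2. The arms are still examined unequally often.

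**3. The plan's own figure.** Sample size asks for more than 30 per group and allows 5 to 10% dropout, giving 36 per group (72 in total). With n/(1 − d) rounded up, 32/(1 − 0.10) = 35.6, so 36. In the other direction, 36 × 0.90 = 32.4 and 36 × 0.95 = 34.2 completers per group. The figure reproduces and is not disputed; it supplies the n below.

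**4. Illustration of rater bias.** Assumptions: no true effect, 32 per group, two-sided 0.05, and a rating shift of b standard deviations of the change score between the arms. The documents give neither a SOAP standard deviation nor a size of bias, so b is shown over a range.

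Rejection probability = P(|T| > t(0.975; 62)), where T is noncentral t with 2 × 32 − 2 = 62 degrees of freedom and noncentrality b × √(32/2) = 4b.

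| Shift b (SD) | Noncentrality | False-positive rate |
|---|---|---|
| 0 | 0 | 5% |
| 0.1 | 0.4 | 6.8% |
| 0.2 | 0.8 | 12% |
| 0.3 | 1.2 | 22% |
| 0.4 | 1.6 | 35% |
| 0.5 | 2.0 | 50% |

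**The case against.** A reader might infer more: that group B has no baseline SOAP at all, so that none of its 36 patients can contribute a change score and the planned test cannot be run. The documents do not support that.
- The timing statement is a note to a figure that is not shown. The Instruments section refers to that figure for the evaluations at baseline and both later visits in both groups, so its cells may mark a T1 SOAP for group B.
- Secondary outcomes names T1 and T3 for this endpoint without restricting it to group A, and defines T3 for both groups.
- The note does not name T1 for group A either, so it may be shorthand that adds the session-by-session forms to the ordinary visits.
- The section describing the osteopath pair is headed for group A and would naturally be silent on group B. The rule that assessors do not treat is not limited to one arm.

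All of this stands, and it limits the timing point to a mismatch in the text that needs clearing up. It is also fair that this is one secondary outcome in a trial that calls itself exploratory, and that the size of any bias is unknown.

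None of it touches the blinding point, which follows from the two sections on who rates and who is told. Nor is this a detail to leave to an analysis plan: the article itself fixes who rates and who knows the arm, and no analysis can blind a rating afterwards.

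**Conclusion.** The concern holds in two parts of different strength.

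**Firm:** the between-arm SOAP test uses ratings that, in group A, come from an osteopath who knows the allocation, and the stated guarantee of independence does not follow from the rater not treating.

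**Qualified:** the readable text gives no baseline time point and no rater for group B, although the planned comparison needs both. Fig. 2 may supply the time point, so this is a gap in the description and not proof of a missing measurement.

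The size of the bias cannot be derived from the documents. Under the stated assumptions, shifts of 0.1 to 0.5 SD would take the false-positive rate from the nominal 5% to between about 7% and 50%. The damage is confined to the somatic-dysfunction claim; the primary fMAIA analysis and the sample size are not affected. The change should be made, but the trial does not stand or fall on it.

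**What to change.** **Preferred.** State that the between-arm comparison uses SOAP at T1 and T3 only, in both arms. Have both ratings made by an already trained osteopath student who is not told the allocation and does not attend that patient's sessions, and take T1 before randomisation. The pair's session-by-session forms can continue in group A but stay out of the comparison. Amend the Blinding section so that it says these raters are unaware of the arm, and name group B's time points and rater.

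Cost: rota changes, and short examinations in group B if they are not already scheduled. It is not fully available for patients already randomised. Trial status says that recruitment and data collection have begun, and a pre-randomisation rating cannot be added afterwards if it was not taken.

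**Where this cannot be done.** Report SOAP as a descriptive outcome, stating that it is open to unblinded-rater bias. Remove the efficacy comparison on somatic dysfunction from Secondary objectives and the SOAP test from Statistical methods. Cost: wording only, and the loss of one inferential secondary claim.

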#### Clinical and demographic information

The patient’s demographic information will be collected through a self-report questionnaire, and clinical information (e.g., personal and family psychiatric history, history of illness, current treatment) will be collected through a semi-structured interview. Weight will be measured with the subject wearing only underwear on the same calibrated scales. Stature will be measured using a stadiometer.

#### Psychological quantitative evaluation

##### Short-CIDI

The Short-CIDI (Composite International Diagnostic Interview) form is a hetero-questionnaire diagnostic assessment instrument for the diagnosis of eating disorder (ED) [32]. The sections of the Short-CIDI relevant for the evaluation of ED will be used.

##### fMAIA scale (Multidimensional Assessment of Interoceptive Awareness, French version).

Interoceptive consciousness is a concept that describes behavioral, metacognitive, and cognitive processes related to internal bodily perceptions. The sub-components are as follows: interoceptive precision, metacognitive interoceptive consciousness, and interoceptive sensitivity [33]. The interoceptive sensitivity is concerned with the cognitive beliefs of the subjects in relation to their bodily perceptions. It is measured through certain scales such as MAIA (Multidimensional Assessment of Interoceptive Awareness) [34]. MAIA is a 32-item multidimensional scale with 8 sub-scales: (a) Noticing: awareness of uncomfortable, comfortable and neutral bodily sensations; (b) Not-Distracting: the tendency to not ignore or distract oneself from sensations of pain or discomfort; (c) Not-Worrying: the tendency to not react with emotional distress or worry to sensations of pain or discomfort; (d) Attention Regulation: the ability to sustain and control attention to bodily sensation; (e) Emotional Awareness: the awareness of the connection between bodily sensations and emotional states; (f) Self-Regulation: the ability to regulate psychological distress by attention to bodily sensations; (g) Body Listening: actively listening to the body for insight; and (h) Trusting: experiencing one’s body as safe and trustworthy. The scale was studied in an ED clinical population including restrictive AN, AN with purging behaviors, bulimia, bulimic hyperphagia, Avoidant Restrictive Food Intake Disorder (ARFID), and other specified EDs [35]. In this study, the dimensions of not-distracting, self-regulation, body listening, and trusting were more strongly associated with ED [35]. This scale was translated and validated in French, presented at the congress of the French Society of Psychology in 2016 [36]. The translated scale has good psychometric properties. The results show that the fMAIA follows a factor structure similar to that of the original version. The internal consistency is good (*α* = 0.83), as well as its stability over time.

##### Eating Disorder Diagnostic Scale (EDDS)

The Eating Disorder Diagnostic Scale (EDDS) is a self-administered questionnaire of 23 items used to assess the presence of AN, bulimia nervosa, and binge-eating disorder [37]. The scale is presented as a combination of questionnaires with Likert scales, yes/no scores, frequency scales, and open-ended questions.

##### Eating Disorders Inventory (EDI-2)

The Eating Disorders Inventory-2 (EDI-2) is intended to assess attitudes and behaviors related to eating habits [38, 39]. Although it is not diagnostic, it is often used in the context of a search for an ED to study the psychological characteristics of the subjects. Eleven dimensions are listed: drive for thinness, bulimia, body dissatisfaction, ineffectiveness, perfectionism, interpersonal distrust, interoceptive awareness, fear of maturity, asceticism, impulsivity regulation, and social insecurity. Each of the 91 items must be rated by the subject in six degrees ranging from “never” to “always.” Higher scores indicate higher level of symptoms.

##### Body Shape Questionnaire (BSQ)

The Body Shape Questionnaire (BSQ) is a one-dimensional self-assessment of 34 items used to assess preoccupations and concerns around body image, developed by Cooper and his colleagues and validated in French [40, 41]. The BSQ-34 scale includes four sub-scales: body dissatisfaction, fear of gaining weight, low self-esteem, and desire to lose weight. A high score indicates strong body image concern. The 34 items refer to the status of the last 4 weeks and the answers are in the form of a 6-point Likert scale from “never” to “always.” The total score ranges from 34 to 204. Scores below 80 indicate a lack of clinical significance of bodily concerns.

##### Bermond-Vorst Alexithymia Questionnaire Form B (BVAQ-B)

The Bermond-Vorst Alexithymia Questionnaire Form B (BVAQ-B) is a self-administered questionnaire that evaluates introspection and emotional regulation difficulties [42, 43]. This is a questionnaire of 20 items including 5 sub-scales: verbalization of emotional experiences (B1), waking dream and fantasies (B2), identification of emotions (B3), tendency to be awakened by events inducing emotions (B4), analysis of one’s own emotional states and reactions (B5). A high score indicates a high level of alexithymia.

##### Rosenberg Self-Esteem Scale (RSE)

The Rosenberg Self-Esteem Scale (RSE) is one of the most well-known and widely used scales in self-esteem assessment [44, 45]. This scale proposes ten items: five correspond to high self-esteem, and five correspond to low self-esteem. For each of the questions asked, the subject gives his appreciation on a Likert scale in four points ranging from “fully agree” (1) to “do not agree at all” (4). For positive questions, the score is added up. For negative questions, the rating is reversed. Possible scores range from 10 to 40, 40 representing the highest level of self-esteem, while 10 represents the lowest level of self-esteem. A score of 10 to 16 is in favor of low self-esteem, a score of 17 to 33 is an average self-esteem, and finally, a score of 34 to 40 shows high self-esteem.

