#### Statistical methods

##### Quantitative data

First, we will conduct descriptive analyses (calculations of means and standard deviation for the quantitative variables, percentages, and absolute numbers for the qualitative variables).

Quantitative variables will be analyzed with Student’s *t* test or a Mann-Whitney rank test if the validity conditions of the Student’s test are not validated. That will include the primary outcome as the difference between the fMAIA values between the last and the first evaluations, and the secondary outcomes such as the change in the patient’s clinical outcome (weight, pain…), the change in the nature and severity of patient’s ED symptoms (EDDS and EDI-2), the change in the nature and severity of patient’s psychopathological symptoms (BSQ, BVAQ, RSE, STAI-Y, DEQ, HAD, OSI, EDS-R), the change in the perceived quality of life (ED-QOL), and the change in somatic dysfunction (SOAP note form) from T1 to T3.

Qualitative variables will be analyzed with a chi-square test or an exact Fisher test if the validity conditions for chi-square are not validated. That will include the socio-demographic data and some secondary outcomes such as the change in the patient’s clinical outcome (localization of pain, transit…) from T1 to T3. Statistical tests will be two-sided with a significance level set at 0.05.

Relative to sample size, we did not plan any adjusted or additional analyses. In addition, we will collect different information for each patient at each stage of the protocol (inclusion, randomization, assessments). Subjects randomized to a group that will ultimately do not join their randomization group will be out of the study. We have estimated for the calculation of the sample size a dropout rate of 5 to 10%, which remains compatible with sufficient statistical power. We will compare the characteristics of dropout subjects compared to those who completed the study to investigate possible biases.

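### The Rosenberg Self-Esteem Scale (RSE) item coding and reversal rule contradict the stated direction of the total; applied literally, they would reverse the sign of this secondary outcome

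*Protocol article*

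**What the plan says.** All the scoring information is in the protocol article, under Instruments, Rosenberg Self-Esteem Scale (RSE). That paragraph fixes five things:

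- Item content: "This scale proposes ten items: five correspond to high self-esteem, and five correspond to low self-esteem".
- Response coding: "a Likert scale in four points ranging from “fully agree” (1) to “do not agree at all” (4").
- Scoring rule: "For positive questions, the score is added up. For negative questions, the rating is reversed".
- Range and direction: "Possible scores range from 10 to 40, 40 representing the highest level of self-esteem, while 10 represents the lowest level of self-esteem".
- Interpretation bands: "A score of 10 to 16 is in favor of low self-esteem, a score of 17 to 33 is an average self-esteem", with 34 to 40 classed as high.

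The RSE is a secondary outcome. The Secondary outcomes section lists change in "psychopathological symptoms (BSQ, BVAQ, RSE, STAI-Y, DEQ, HAD, OSI, EDS-R) from T1 to T3". The Quantitative data section under Statistical methods has that change compared by Student's t test or, failing its conditions, the Mann-Whitney test, two-sided at 0.05. No other section gives a different RSE coding.

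**The concern.** Agreement carries the low code. Adding the positive items as rated therefore gives a small sum to a patient who endorses them, and reversing the negative items pulls those the same way. The total then falls as self-esteem rises, while the paragraph says that it rises.

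What is at stake is the direction of one between-group comparison. If someone programmed the scoring from this paragraph and read the result with the stated direction, a gain in self-esteem would be reported as a loss, and a loss as a gain. Two features of the article make such a slip hard to notice:

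- Data collection and management gives out-of-range values as its example of detectable errors, but wrongly directed totals still lie between 10 and 40.
- The scales in the battery do not share a direction. A high score is unfavourable on the BSQ and the BVAQ-B but favourable on the ED-QOL, so the sign of the RSE result cannot be checked against a common convention.

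**Working it through.** **Inputs**, all from the RSE paragraph: five positive items with ratings p₁…p₅; five negative items with ratings n₁…n₅; ratings from 1 (full agreement) to 4 (complete disagreement). Reversing a 1-to-4 rating means 5 − rating.

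**Score as written:** L = Σp + Σ(5 − n).

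**Step 1: the stated range.** The smallest possible L is 5×1 + 5×1 = 10 and the largest is 5×4 + 5×4 = 40. The stated range of 10 to 40 is reproduced.

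**Step 2: the stated direction.** The highest self-esteem means full agreement with every positive item (p = 1) and complete rejection of every negative item (n = 4). The lowest is the opposite pattern (p = 4, n = 1).

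- Highest: L = 5×1 + 5×(5 − 4) = 5 + 5 = 10. Stated: 40.
- Lowest: L = 5×4 + 5×(5 − 1) = 20 + 20 = 40. Stated: 10.

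The direction is not reproduced.

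**Step 3: other readings.**

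| Reading | Highest self-esteem | Lowest self-esteem | Agrees with stated direction? |
|---|---|---|---|
| As written | 10 | 40 | No, opposite |
| No item reversed | 25 | 25 | No, extremes coincide |
| Positive items reversed, negative as rated | 40 | 10 | Yes |
| Full agreement = 4, complete disagreement = 1, rule unchanged | 40 | 10 | Yes |

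The two readings that agree each require a change to the printed text.

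**Step 4: relation between the two totals.** A total running in the stated direction is I = Σ(5 − p) + Σn. Adding it to L gives L + I = Σ5 + Σ5 = 25 + 25 = 50. So L = 50 − I for every complete questionnaire.

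**Step 5: effect on the analysis.** For the change from T1 to T3, ΔL = (50 − I₃) − (50 − I₁) = −ΔI. The constant cancels and only the sign flips. The SD of the change is the same, the absolute difference between groups is the same, the t statistic changes sign only, and the rank test is mirrored. Two-sided p values are identical. As an illustration with an assumed figure, a true between-group difference of +4 points would appear as −4 with the same p value.

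**Step 6: effect on the bands.** Under 50 − I, the band 10–16 maps to 34–40, 34–40 maps to 10–16, and 17–33 maps to itself. Only patients in the two outer bands would be mislabelled.

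**The case against.** The best defence is that this is a descriptive paragraph in a journal article and not a scoring program. The intended direction is stated twice, once through the endpoints and once through bands that agree with them, so the meaning of a high score is clear. The slip is then confined to the printed coding or to the reversal sentence, and the working code may be correct. The statistical methods text says only that the RSE change is compared; it contains no item-level scoring.

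Much of this stands. A reader might infer that the trial's self-esteem result is, or will be, reversed. The article does not support that, because nothing in it shows how the questionnaires are actually scored or which of the printed statements is the faulty one. A reader might also infer that mislabelled categories would distort an analysis. The planned RSE comparison is of the change in score, and no planned analysis uses the bands. Nor does the place of self-esteem at the head of the list in the secondary objectives make it a leading outcome: no hierarchy is stated, the RSE is one of eight instruments in its secondary-outcome item, and the trial calls itself exploratory.

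The defence does not remove the contradiction. The article chose to print coding, rule, range, direction and bands, and they conflict. This is a wrong statement and not a detail left to a fuller document.

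**Conclusion.** The point holds as an internal contradiction in the RSE scoring description, provable from that one paragraph. Its consequence is conditional. If the coding and rule are applied as printed and the total is read in the stated direction, every complete total is 50 minus the intended one, the RSE change has the wrong sign, and the low and high labels swap. Magnitude, SD and two-sided p value are untouched. The fMAIA primary outcome and the sample size do not depend on it.

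The conclusion assumes only that reversal means 5 − rating on the 1-to-4 scale and that questionnaires are complete. It says nothing about whether any data have been mis-scored. It merits correction because the outcome is formally tested, a sign error would survive a range check, and the Trial status section reports that data collection had already begun.

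**What to change.** Make the paragraph consistent in one of two equivalent ways:

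- code full agreement as 4 down to complete disagreement as 1, and keep the reversal of the five negative items; or
- keep the printed 1-to-4 coding, reverse the five positive items, and add the negative items as rated.

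Choose whichever matches the numbers printed on the questionnaire that patients complete. Before analysis, check that form and the scoring code against the corrected rule. Scoring the two extreme answer patterns is a sufficient test of direction: highest self-esteem must return 40 and lowest 10. Apply 50 − score only to totals shown to have been computed by the literal rule. Applied to correctly scored totals, the conversion would itself create the reversal.

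The cost is one sentence in the protocol and one check of the form and code. No change to design, data collection or sample size is needed.
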